**Figure 3 ijerph-18-00226-f003:**
[figure not shown]
Assignment of participants and completed follow-up: flow diagram based on CONsolidated Standards of Reporting Trials (CONSORT) [28].

**Figure 4 ijerph-18-00226-f004:**
[figure not shown]
Map of study area with points marking the location of study schools. The map shows the study area in the National Capital Region, also known as Metro Manila, in northern Philippines, with study schools plotted as points. The red pushpin marker in the lower left inset map indicates where the location of the study area is within the Philippines, specifically in the northern most island group of Luzon.

**Table 1 ijerph-18-00226-t001:** Operational definitions.

Indicator		Definition	Reference
Malnutrition			
Stunting	Stunted	HAZ < −2	[4,31,32]
Undernutrition	Underweight (“thin”)	−3 < BAZ < −2	[4,29,30]
	Wasted (“severely thin”)	BAZ < −3	[4,29,30]
Over-nutrition	Overweight	1 < BAZ < 2	[4,29,30]
	Obese	BAZ > 2	[4,29,30]
Acute dehydration Concentrated urine Moderately concentrated urine Severely concentrated urine WaSH adequacy		sg ≥ 1.020 sg = 1.025 sg = 1.030	[33] Category used in present study Category used in present study
Sanitation			
Improved	Facility that hygienically separates human excreta from human contact	e.g., flush toilet, pour-flush latrines, ventilated improved pit latrines and pit latrines with a slab or covered pit	[34]
Unimproved	Facility that does not hygienically separates human excreta from human contact	e.g., pit latrines without slabs or platforms or open pit, hanging latrines, bucket latrines, open defecation, disposal of human feces with other forms of solid waste	[34]
Male student-to-toilet ratio	Less than 50 students	1 toilet, 1 urinal, 1 handwashing basin	[35]
	50 or more students	2 toilets, 1 urinal, 2 handwashing basins	[35]
	For each additional 100 students	1 toilet, 1 urinal, 1 handwashing basin	[35]
Female student-to-toilet ratio	Less than 30 students	1 toilet, 1 handwashing basin	[35]
	30–100 students	2 toilets, 2 handwashing basins	[35]
	For each additional 50 students	1 toilet	[35]
	For each additional 100 students	1 handwashing basin	[35]
Male student-to-toilet ratio	50 students	1 toilet, 1 urinal (or 50 cm of urinal wall)	[36]
Female student-to-toilet ratio	25 students	1 toilet	[36]
Student-to-handwashing basin ratio	N/A	N/A	No WHO guidelines available
Male student-to-toilet ratio	Low	≤ 50:1	Category used in present study
	Medium	51:1–100:1	Category used in present study
	High	≥ 101:1	Category used in present study
Female student-to-toilet ratio	Low	≤ 50:1	Category used in present study
	Medium	51:1–100:1	Category used in present study
	High	≥ 101:1	Category used in present study
Student-to-handwashing basin ratio	Low Medium High	≤ 50:1 51:1-150:1 ≥151:1	Category used in present study Category used in present study Category used in present study

Note: body mass index (BMI); body mass index-for-age Z-score (BAZ); Department of Health Philippines (DOH); height-for-age Z-score (HAZ); not applicable (N/A); urine specific gravity = U_sg_; water, sanitation, and hygiene (WaSH); weight-for-age Z-score (WAZ); World Health Organization (WHO).BAZ is BMI, which is calculated by weight (kg)/[height (m)]^2^. We measured BAZ instead of WAZ because the latter is appropriate only for children < 5. We used BAZ and HAZ measurements, along with children’s age, to calculate anthropometric indices, which were computed as Z-scores (the number of standard deviations [SDs] in relation to the mean of the standard population). When computing Z-scores, we referred to the 2007 WHO database for child growth standards [4,29,30,31,32,33]. We used the WHO AnthroPlus (for children 5–19 years old) software (version 3.2.2., WHO, Geneva, Switzerland) to obtain HAZ and BAZ for each child. We defined acute dehydration as having highly concentrated urine defined as urine sg ≥ 1.020 [33]. We measured urine sg via point-of-care urinalysis using urine test strips as described in Figure S3. We measured urine sg as a continuous variable and as a binary variable: concentrated urine, sg ≥ 1.020 (yes/no), moderately concentrated urine, sg = 1.025, and highly concentrated urine, sg = 1.030). Urine sg estimates the ratio of solutes (e.g., electrolytes, nitrogenous chemicals) compared with distilled water, which has a sg of 1.000. The normal range of urine sg is 1.003–1.030, with higher numbers indicating a greater concentration of solutes and, consequently, decreased hydration (known as “dehydration”) [33]. The gold standard for measuring urine sg is urine osmolality, although this test is invasive, expensive, and not practical in field settings. We defined children as dehydrated if urine sg ≥ 1.020. This cutoff corresponds to a urine osmolality of > 800 mOsm/kg H_2_O, which is the cutoff used in previous studies involving dehydrated children [37,38].

**Table 2 ijerph-18-00226-t002:** Data collection during the WaSH in Manila Schools project.

Instrument	Types of Data Collected	Frequency and Time Period (s)
WaSH-related knowledge, attitudes, and practices (KAP) questionnaire for children	Self-reported: Demographics Perceptions about and use of school WaSH facilities Hygiene behavior (e.g., handwashing) Health history Food security	1 time: February–March 2017
Health examination (form) for children	Observed: Height Weight Urine specific gravity	3 times: February–March 2017; different sample of students during June–July 2017 and February–March 2018
Interview (form) for school principal ^(1)^	Self-reported: Perceptions about school WaSH facilities and students’ hygiene WaSH-related policies	2 times: March–June 2017; November–December 2018
School restroom inspection checklist	Observed: Availability, quantity, and quality of school WaSH facilities	2 times: February–March 2017; September–December 2018
Interview (form) for parent/guardian	Self-reported: Demographics Food security Hygiene behavior (e.g., handwashing)	1 time: March–June 2017
Home restroom inspection checklist	Observed: Availability and quality of home WaSH facilities	1 time: March–June 2017
Health literacy questionnaire for children	Self-reported: Demographics Understanding of hygiene concepts and handwashing	2 times: June–July 2017 and February–March 2018
Handwashing observation form	Observed: Children’s handwashing behavior	2 times: October 2017; February–March 2018
Water quality testing form	Observed: Indicators of water quality	1 time: April 2018 ^(2)^
Household questionnaire for children	Self-reported: Demographics Perceptions about school and home WaSH facilities Hygiene behavior (e.g., handwashing) Health and nutrition status Food security Exposure to second-hand smoke Home and household characteristics Parent/guardian’s education and employment	1 time: November 2018–February 2019
N/A	Secondary school administration data ^(3)^	Various

Note: Department of Education Philippines (DepEd); Philippines Department of Health (DOH); knowledge, attitudes, and practices (KAP); maintenance and other operating expenses (MOOE); water, sanitation, and hygiene (WaSH); World Health Organization (WHO).We assessed risk factors for desired outcomes at the individual-, school-, and home-levels. At the individual-level, we assessed demographics, self-reported health status, history of extreme hunger (e.g., feeling too hungry to fall asleep), exposure to secondhand smoke at home, and perceptions of school WaSH facilities. At the school-level, we measured the adequacy of WaSH facilities by counting the number and assessing the quality (e.g., cleanliness, functionality) of toilets, urinals, and handwashing units. We estimated student-to-toilet and student-to-handwashing unit ratios based on the DOH guidelines (Table 1). We decided not to base our estimations on the WHO guidelines (Table 1) because public schools in many parts of the Philippines, similar to other LMICs, currently have limited capacity to effectively address the over-crowding of students on school campus. We asked school principals about WaSH-related school policies, e.g., “Is there a school policy to clean the students’ restrooms daily?” [27]. We retrieved secondary school administrative data from school secretaries and the DepEd. At the household-level, we assessed the family’s demographics (e.g., the number of adults and children in the home), food insecurity, experience of having to ask/beg for food; parent’s employment status, education, literacy, history of physical or intellectual disability; access to and adequacy of the home’s WaSH facilities. To assess the family’s socioeconomic status we examined ownership of household appliances and electronic devices (e.g., refrigerator, mobile phone), ownership of transportation vehicles, most frequently used mode of transportation to school, material of the home’s flooring, and availability of electricity. Eight months after implementing the intervention, we revisited children from the control and intervention arms for a follow-up assessment that used the same study design as the baseline assessment. We used the same survey instruments that we used in the previous observational study [4] to measure: children’s health literacy and nutrition outcomes, handwashing prevalence, school restrooms’ WaSH adequacy, and schools’ WaSH policies. Seventeen months after implementing the intervention, we administered a household questionnaire for children, some of whom had graduated and/or transferred to different schools since participating in the previous follow-up assessment. ^(^^1)^ Some school principals had left their respective schools by the time we conducted our follow-up interviews. Thus, the pre- and post-intervention samples of school principals were not comprised of the exact same individuals for all schools. ^(2)^ In our analyses, we included secondary water quality testing data that was collected in 2016 for one school from the control arm. ^(3)^ School administration data: e.g., enrollment, number of classrooms, and MOOE budget.

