#### 2.5.2. Assessing Secondary Intervention Outcomes

First we assessed children’s overall health status, extreme hunger prevalence, and satisfaction with and perceived cleanliness of schools’ WaSH facilities, measured by binary variables, via questionnaire (Table S6). We assessed acute dehydration, measured by incidence of highly concentrated urine (U_sg_ ≥ 1.020) [33,37,38] (Table 1), via urinalysis using urine test strips (Insight Urinalysis Reagent Strips, Acon Laboratories Inc., San Diego, CA, USA). Urine test strips are an affordable, easy to use, and reliable way to perform urinalysis in field settings [39]. Second we assessed school principals’ satisfaction with schools’ WaSH facilities and children’s hygiene practices, measured by binary variables, via interview. Third we assessed, via observation, schools’ WaSH adequacy, measured by continuous and binary variables describing availability, accessibility, cleanliness, and functionality, according to guidelines from the Philippines DepED and Department of Health (DOH) [35,40]. We previously reported the data collection tools we used for conducting health examinations, interviews with school principals, and school restroom inspections [27]. Data collection tools were pilot-tested and improved prior to beginning this trial.

During our previous observational study, we found that children were avoiding or not using school restrooms, possibly due to a perceived lack of cleanliness or lack of privacy. Findings indicated that avoidance and non-use of school restrooms increased children’s risk of diarrhea. Thus, we aimed to see if our intervention was effective in improving children’s perceptions about school restrooms, with the hope that children would use school restrooms rather than avoid using them. Also, we found that school WaSH policies were in place, yet school principals reported being unsatisfied with WaSH facilities and children’s hygiene behaviors. School principals’ perceptions about WaSH could affect efforts to implement, maintain, and sustain improvements, all of which influence children’s health and hygiene behaviors. Thus, we aimed to see if our intervention was effective in improving school principals’ perceptions about school WaSH facilities.

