#### 2.5.4. Follow-Up and Other Assessments

Eight months later, we conducted a follow-up assessment by implementing the same methodology (i.e., 4-part school-based survey) that we used at baseline (Figure S3) and measuring the same types of outcomes (e.g., children’s health literacy and nutrition status, handwashing prevalence, school restrooms’ WaSH adequacy, and schools’ WaSH policies). Nine months later (17 months after the first health education session), we conducted a household questionnaire for children (Table S5). Thus, we were able to assess risk factors at the individual-, school-, and home-levels (Table 2).

We expected the intervention to influence children’s knowledge, behavior, and health outcomes. We defined indicators of the intervention’s impact as changes in children’s primary and secondary outcomes. We measured the difference between outcomes from the eight-month follow-up and baseline. We compared differences between control and intervention arms. We collected samples for water quality testing from study schools and a separate sample of households (located in the school neighborhood) after post-intervention assessments, as previously reported [27].

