**Figure 2 ijerph-18-00226-f002:**
[figure not shown]
WaSH in Manila Schools project aims and timeline. Note: water, sanitation, and hygiene (WaSH). (**a**) Aims of overall project, observational study, and longitudinal study. (**b**) Timelines for observational study and longitudinal study, including research activities. ^(1)^ Please see References [27]. ^(2)^ Eight months after implementing the intervention, we revisited children from the control and intervention arms for a follow-up assessment that used the same study design as the baseline assessment. We used the same survey instruments to measure: children’s health literacy (Tables S3 and S4) and health and nutrition outcomes; children’s handwashing prevalence; school restrooms’ WaSH adequacy; and schools’ WaSH policies. ^(3)^ In November 2018, 17 months after implementing the intervention, we administered a household questionnaire for children (Table S5), some of whom had graduated and/or transferred to different schools. We completed the household questionnaire in February 2019.

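### Text and Table 2 conflict on when restroom, policy and child-reported secondary outcomes were measured; if Table 2 is right, their 8-month change cannot be formed

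*Protocol article*

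**What the plan says.** Section 2.5.4 (Follow-Up and Other Assessments) describes the second visit: "Eight months later, we conducted a follow-up assessment by implementing the same methodology (i.e., 4-part school-based survey) that we used at baseline". Among the things measured there it lists "handwashing prevalence, school restrooms’ WaSH adequacy, and schools’ WaSH policies". The Figure 2 legend and the note under Table 2 say the same. Section 2.5.4 then sets the contrast. "We defined indicators of the intervention’s impact as changes in children’s primary and secondary outcomes", and "We measured the difference between outcomes from the eight-month follow-up and baseline". These differences are to be compared between arms.

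Section 2.5.3 places the restroom inspection and the principal interview in the trial's baseline survey, after data had been obtained from the children.

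Section 2.5.2 lists the secondary intervention outcomes. They include children's overall health status, extreme hunger and "satisfaction with and perceived cleanliness of schools’ WaSH facilities, measured by binary variables, via questionnaire", together with principals' satisfaction, restroom adequacy and urine concentration.

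Table 2 gives the dates:

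- Restroom checklist: "2 times: February–March 2017; September–December 2018".
- Principal interview (perceptions and policies): "2 times: March–June 2017; November–December 2018".
- KAP (knowledge, attitudes and practices) questionnaire for children (facility perceptions, health history, food security): once, February–March 2017.
- Household questionnaire for children (facility perceptions, health and nutrition status, food security): once, November 2018 to February 2019.
- Health literacy questionnaire: June–July 2017 and February–March 2018, listed with demographics and understanding of hygiene and handwashing only.

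By the time of the household questionnaire the children included "some of whom had graduated and/or transferred to different schools" (Figure 2 legend).

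**The concern.** The trial's pre/post contrast is tied to an 8-month interval, but the data-collection table shows no 8-month round for two of the instruments that the text says were repeated then. If the table is right, an analyst who follows section 2.5.4 would either find no data or report late-2018 school data as 8-month effects. Delivery of the intervention ended in February 2018 (section 2.6), so an end-of-intervention effect and an effect several months later are different quantities.

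The child-reported outcomes raise a further problem. On Table 2, their only pre-intervention measurement was in the observational study, whose students were not re-recruited (section 2.3). A change score for health, hunger or facility satisfaction would then subtract one set of children from another. Some children had also changed school by the later questionnaire, so some facility ratings may concern a school outside the trial.

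**Working it through.** **Inputs.** Intervention period June 2017 to February 2018 (section 2.6). Instrument dates from Table 2. Non-re-recruitment of the observational-study students from section 2.3. All intervals are differences in calendar months. For a gap between two rounds, the shortest runs from the last month of the first round to the first month of the second, and the longest from the first month to the last.

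**The plan's own intervals reproduce.**
- June 2017 to February 2018 = 8 months; July 2017 to March 2018 = 8 months.
- June 2017 to November 2018 = 17 months = 8 + 9, as section 2.5.4 states for the household questionnaire.

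The 8-month label is therefore correct for the instruments dated June–July 2017 and February–March 2018: the health literacy questionnaire and the trial rounds of the health examination.

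**Restroom checklist.**
- Between rounds: March 2017 to September 2018 = 18; February 2017 to December 2018 = 22. Gap 18–22 months.
- Second round after the June 2017 start: to September 2018 = 15; to December 2018 = 18.
- Second round after the 8-month visit: March to September 2018 = 6; February to December 2018 = 10.
- First round before the children's baseline: March to June 2017 = 3; February to July 2017 = 5. This conflicts with section 2.5.3, which has the inspection follow the children's data collection.

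**Principal interview.**
- Between rounds: June 2017 to November 2018 = 17; March 2017 to December 2018 = 21. Gap 17–21 months.
- Second round after the June 2017 start: 17–18 months.
- Second round after the 8-month visit: March to November 2018 = 8; February to December 2018 = 10.

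**Child-reported health, hunger and facility perceptions.** I take Table 2's food security entry as the place where extreme hunger would sit.
- Trial visits for which Table 2 lists an instrument with these items: 0 of 2.
- KAP to household questionnaire: March 2017 to November 2018 = 20; February 2017 to February 2019 = 24. Gap 20–24 months, in different children.
- Household questionnaire after the June 2017 start: to November 2018 = 17; to February 2019 = 20.

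**Urine specific gravity.** It belongs to the health examination, which Table 2 dates at both trial visits. Its 8-month change can be formed.

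**The case against.** Three places in the text (section 2.5.4, the Figure 2 legend and the note under Table 2) agree that restroom adequacy and policies were measured at 8 months, so the table may be what is wrong. That stands. A reader might infer that these outcomes were simply not measured at 8 months, but the documents show only that the two accounts cannot both be right.

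The child-reported part rests on short summaries in Table 2. The questionnaires themselves (Tables S3 and S4) are supplementary and not shown, so additional items in the health literacy questionnaire cannot be excluded. The note under Table 2 says that instruments from the observational study were reused at follow-up, and the Figure 2 legend mentions health outcomes. This also stands in part, and it rules out a flat statement that no trial child has paired data. Against it, Table 2 gives the KAP questionnaire one round only, the health examination could account for the legend's wording, and the four-part baseline list in section 2.5.3 names neither health status, hunger nor satisfaction. Section 2.5.2 points to Table S6 for these outcomes, but section 2.3 cites the same table for school compensation, so the pointer does not settle the matter.

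A reader might also infer that the late-2018 inspections are to serve as exposures for the February–March 2018 child outcomes. Nothing says so: section 2.8.2 gives only a generic exposure term, and the models are in Box S2, not shown.

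The article does disclose that some children had moved and some principals had changed. Model C in section 2.8.2, for health status and hunger, is a logistic risk-factor model that needs no change score. Both points are fair, but neither resolves the dates or the contrast in section 2.5.4.

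**Conclusion.** The contradiction is real and should be resolved before results are labelled. For the restroom checklist and principal interview, the text and Table 2 disagree outright. For the child-reported outcomes, the stated contrast needs measurements that Table 2 does not list; confidence here is lower because the instruments are not shown.

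Conditional on Table 2, the 8-month minus baseline difference cannot be formed for restroom adequacy, principal-reported policies and satisfaction, or child-reported health, hunger and facility satisfaction. The school-level outcomes still have a pre/post pair, at a later horizon: about 15–18 months after the June 2017 start for restrooms and 17–18 for principals, or 6–10 and 8–10 months after the 8-month visit. Principal interviews ran into June 2017, the month in which the intervention began, so the first round is pre-intervention only approximately. The child-reported outcomes have one trial measurement, at about 17–20 months.

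These are secondary outcomes. The finding does not touch urine specific gravity or the 8-month interval for the health literacy questionnaire and anthropometry.

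**What to change.** Reconcile sections 2.5.3 and 2.5.4, the Figure 2 legend and the note under Table 2 with the dates in Table 2, and state which instrument carried each child-reported secondary outcome and when. If the text proves right, correct Table 2, and the contrast stands for the outcomes concerned.

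If Table 2 stands:

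- (a) Report restroom adequacy as a school-level change from February–March 2017 to about 15–18 months after the June 2017 start. Report principal-reported policies and satisfaction as a change from March–June 2017 to about 17–18 months. Do not call either an 8-month effect.
- (b) Analyse child-reported health, hunger and facility satisfaction as post-only comparisons between arms at about 17–20 months, with no change score against the KAP sample. Keep all children as assigned in the main analysis, in line with section 2.8. For facility satisfaction, add a sensitivity analysis limited to children still at their assigned school.

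This takes changes of wording and time-point labels and one added sensitivity analysis; no new data are needed. The price is that no 8-month claim remains for these outcomes and no pre/post claim for the child-reported ones. The post-only comparisons also cannot remove baseline differences in those outcomes, which matters because the two control schools were assigned purposefully (section 2.5.3); the report should say so.
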